**Methods/Design:**

Patients meeting diagnostic criteria for a current or lifetime diagnosis of OCD will be recruited via the research arm of a not-for-profit clinical and research unit in Australia. The minimum sample size for each group (alpha set at 0.05, power at .80) was identified as 29, but increased to 35 to allow for 20% attrition. We will measure the impact of CBM on interpretations bias using the OC Bias Measure (The Ambiguous Scenarios Test for OCD ;AST-OCD) and OC-beliefs (The Obsessive Beliefs Questionnaire-TRIP; OBQ-TRIP). Secondary outcome measures include the Dimensional Obsessive-Compulsive Scale (DOCS), the Patient Health Questionnaire (PHQ-9), The Kessler Psychological Distress Scale (K10), and the Word Sentence Association Test for OCD (WSAO). Change in diagnostic status will be indexed using the OCD Mini International Neuropsychiatric Interview (M.I.N.I) Module at baseline and follow-up. Intent-to-treat (ITT) marginal and mixed-effect models using restricted maximum likelihood (REML) estimation will be used to evaluate the primary hypotheses. Stability of bias change will be assessed at 1-month follow-up.

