The current SPIRIT-compliant [31] protocol (see Table 1) outlines the methodology of a randomized controlled trial (RCT) to establish the efficacy of a CBM intervention for participants who meet current diagnostic status for OCD when compared to an active CBM control condition. In order to investigate whether previously symptomatic individuals demonstrate a negative interpretation bias for OC-specific information, participants with a lifetime diagnosis of OCD will also be recruited for secondary analyses.

**Table 1 T1:** Items from the World Health Organization trial registration data set

**Secondary identifying numbers**	**ACTRN12613001130752**
Source(s) of monetary or material support	
Primary sponsor	St Vincent’s Hospital, Sydney
Secondary sponsor(s)	
Contact for public queries	AW, GA
Contact for scientific queries	AW, GA
Public title	Cognitive Bias Modification (CBM) and Obsessive Compulsive Beliefs
Scientific title	Randomized controlled trial comparing Internet-based cognitive bias modification (active version) for obsessive compulsive disorder versus Internet based cognitive bias modification (control version) on negative interpretation bias.
Countries of recruitment	Australia
Health condition(s) or problem(s) studied	Obsessive Compulsive Disorder
Intervention(s)	Experimental: CBM Version A (Active treatment)
	CBM Version A is an Internet-based intervention taking place over 1 week.
	Placebo Comparator: CBM Version B (Control)
	CBM Version B (Control) is an Internet-based intervention taking place over 1 week (identical to CBM Version A without the putative active components).
Key inclusion and exclusion criteria	Inclusion: 18 to 65 years of age; Meet Diagnostic and Statistical Manual of the American Psychiatric Association - 4th edition (DSM-IV) criteria for current or lifetime Obsessive Compulsive Disorder; Internet and printer access; Australian resident; fluent in written and spoken English
	Exclusion: Current substance abuse/dependence; Psychotic mental illness (Bipolar or Schizophrenia); change in medication or psychological treatment during last 1 month or intended change during study duration; use of Benzodiazepines, severe depression (PHQ9 > 23), Suicidal (PHQ9 item 9 > 2)
Study type	Interventional
Date of first enrollment	24 October 2013
Target sample size	70
Recruitment status	Recruiting

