### Participants and recruitment

Power calculations were informed by calculation of effect size data from Williams and Grisham [30] and Clerkin and Teachman [28] providing between-group effect sizes of .66 and .76, respectively. The minimum sample size for each group meeting current diagnostic status (alpha set at 0.05, power at .80) was identified as 29, but is set at 35 to hedge against expected attrition of up to 20%. Participants will be recruited via the research arm of a not-for-profit clinical and research unit affiliated with St. Vincent’s Hospital and the University of New South Wales, Australia.

Potential participants will be recruited from the community and from previous research trials via advertisements placed on local mental health websites, in newsletters, and in printed newspapers. Applicants will be directed to the Virtual Clinic website (http://www.virtualclinic.org.au) where they first complete automated online screening questionnaires about symptoms and demographic details (see Figure 1). Inclusion criteria are as follows: meet diagnostic criteria for current or lifetime Obsessive Compulsive Disorder; has Internet and printer access; is an Australian resident; and is fluent in written and spoken English. Exclusion criteria are as follows: is a non-resident of Australia; is less than 18 or older than 65 years of age; is currently receiving CBT for OCD; has severe depression and (PHQ9 > 23)/ or suicidal ideation (PHQ9 item 9 = 3); has drug or alcohol dependence; has a psychotic disorder or is taking atypical antipsychotics or benzodiazepines; and if taking medication for anxiety or depression, has been taking the same dose for less than 1 month or intends to change the dose during the course of the program. Excluded applicants receive information on alternative services and are encouraged to discuss their symptoms with their physician.

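### The 35 per arm does not protect the stated minimum of 29 against 20% attrition (it leaves 28), and the plan does not say which effect size or sidedness gives 29

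*Protocol article*

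**What the plan says.** The section "Participants and recruitment" bases the calculation on two earlier studies "providing between-group effect sizes of .66 and .76, respectively". With "alpha set at 0.05, power at .80", the minimum for each group with current OCD "was identified as 29, but is set at 35 to hedge against expected attrition of up to 20" per cent. The Abstract repeats the figures: the minimum "was identified as 29, but increased to 35 to allow for 20% attrition". Table 1 gives a target of 70, which is 2 × 35.

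The paragraph does not give the sidedness of the test, the test itself, or which of the two effect sizes leads to 29. The Background adds that "participants with a lifetime diagnosis of OCD will also be recruited for secondary analyses". The Statistical methods section plans intention-to-treat mixed models with REML to deal with drop-out.

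**The concern.** Two things in one short paragraph do not fit together.

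- **Attrition.** The allowance is meant to keep at least 29 per arm after losses of up to 20%. It fails at that ceiling by the plan's own figures, whatever test or effect size is assumed.
- **Effect size.** Two planning effects are cited and one sample size is given. A reader may take 80% power to hold for both. Under the usual two-sided test it holds for the larger only. The smaller effect comes from the study in which, according to the Interventions section, these training modules were validated.

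What is at stake is how a null result would be read. If the sample was sized on 0.76, it is less informative about an effect of 0.66 than the stated 80% suggests.

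**Working it through.** **Inputs.** From Participants and recruitment: alpha 0.05, power 0.80, d = 0.66 and 0.76, minimum 29 per group, planned 35 per group, attrition up to 20%. Assumed: 1:1 allocation (two parallel arms with the same n per group) and an unadjusted two-sample t-test. Sidedness is not stated, so both versions are shown.

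**Step 1: reproduce 29.** The required n per arm solves power(d, n, alpha) = 0.80 under the noncentral t distribution with 2n − 2 degrees of freedom and noncentrality d·√(n/2).

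| Effect | Sidedness | n for 80% | Rounded up |
|---|---|---|---|
| 0.76 | two-sided | 28.17 | 29 |
| 0.66 | two-sided | 37.02 | 38 |
| 0.66 | one-sided | 29.09 | 30 (29 by normal approximation) |

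The plan's 29 is reproduced exactly by 0.76 two-sided, and nearly so by 0.66 one-sided. It is not reproduced by 0.66 two-sided.

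**Step 2: reproduce 35.** 29 × (1 + 0.20) = 34.8, so 35. The inflation that leaves 29 after 20% loss is 29/(1 − 0.20) = 36.25, so 37.

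**Step 3: check 35 against the stated attrition.** 35 × 0.80 = 28, below 29. The largest loss that still leaves 29 is 1 − 29/35 = 0.171, about 17%.

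**Step 4: power at the relevant sizes** (t-test, alpha 0.05).

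| n per arm | d = 0.76, two-sided | d = 0.66, two-sided | d = 0.66, one-sided |
|---|---|---|---|
| 28 (35 less 20%) | 79.8% | 67.9% | 78.6% |
| 29 (stated minimum) | 81.2% | 69.5% | 79.9% |
| 35 (no loss) | 88.0% | 77.7% | 86.2% |

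At 0.76 the inflation slip costs 81.2 − 79.8 = 1.4 points. The choice of effect size costs more: at 28 per arm, 79.8 − 67.9 = 11.9 points between the two planning effects.

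**Step 5: sensitivity to the planned analysis.** The documents give no correlation between repeated measurements, so this is an illustration only. Assume a pre-post correlation r and 28 complete cases per arm at d = 0.66. A change-score analysis has effective d = 0.66/√(2(1 − r)). A baseline-adjusted analysis has effective d = 0.66/√(1 − r²).

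- r = 0.5: change score 0.66, power 68%; baseline-adjusted 0.76, power 80%.
- r = 0.7: change score 0.85, power 88%; baseline-adjusted 0.92, power 92%.

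For r below 0.5 a change-score analysis does worse than the unadjusted comparison.

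**The case against.** **The attrition slip is nearly harmless.** At d = 0.76, 28 per arm still gives 79.8%, and 20% is worded as a ceiling. This stands. A reader might infer that the slip alone takes away the stated 80% power; the figures do not support that. What remains is that the stated purpose of the 35 is not met.

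**The test may be one-sided.** The Hypotheses section is directional, and one-sided 5% at 0.66 needs 29.09 per arm. This stands as a possibility, so it cannot be said without a condition that 29 suffices for the larger effect only. But directional hypotheses do not declare a one-sided alpha, and nothing in the article does.

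**Citing two effects does not promise 80% at both.** That is fair, and it is a reason to say which one was used.

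**The planned analysis is a REML mixed model.** It uses partial data from drop-outs, so 28 complete cases are not the analysed set, and Step 5 shows that power could be higher or lower. A reader might infer that the trial has about a one-in-three chance of missing 0.66. That holds only for an unadjusted two-sided comparison of 28 completers per arm.

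**Do lifetime-only participants use up places in the 70?** A reader might infer that the current-OCD arms will fall below 35. The article does not show this. It ties the per-group size to current OCD, says lifetime participants are recruited in addition for secondary analyses, and gives no expected share of them. A sentence of clarification would help, but no shortfall is shown.

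**Conclusion.** The attrition allowance is wrong as written: 20% loss from 35 leaves 28, not 29, and a minimum of 29 would call for 37. This needs no assumption about the test, and its effect on power at 0.76 is slight.

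The basis of 29 is not identified. Under the conventional two-sided test it corresponds to 0.76, and power at 0.66 lies between about 68% (28 per arm) and 78% (all 35). Those figures rest on an unadjusted two-sample comparison with 1:1 allocation; the mixed model may give more or less. If a one-sided test was meant, 29 is close to right for 0.66.

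This is therefore a mis-stated and incomplete sample-size justification, not proof that the trial is underpowered for its planned analysis.

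**What to change.** Restate the paragraph, and bring the Abstract into line, for example: *35 randomised per arm with current OCD, 28 expected after 20% attrition, gives about 80% power for d = 0.76 and 68% for d = 0.66 (two-sided 0.05, unadjusted two-sample comparison; the planned mixed model may differ).*

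- Name the effect size and sidedness behind 29. If the test was one-sided, say so and give the power on that basis.
- Either correct the inflation (29 evaluable corresponds to 37 randomised per arm, 74 in all) or keep 35 and state that it covers attrition up to about 17%.
- Add to Table 1 whether the target of 70 counts current-OCD participants only.

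The cost is a few sentences. No extra enrolment is needed if the figures are restated, but the stated power becomes less favourable at 0.66. Choosing 37 per arm instead would add four participants (74 − 70).

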**Figure 1 F1:**
[figure not shown]
Study flow chart.

Applicants whose responses to the questions meet selection criteria are telephoned for a diagnostic interview using the M.I.N.I Version 5.0.0 [32] to determine whether they meet criteria for a current or lifetime diagnosis of Obsessive Compulsive Disorder. Applicants who satisfy all inclusion criteria will be informed of the study design and complete an electronic informed consent prior to being enrolled in the trial. All participants are informed in writing that they have right to withdraw from the study at any time without jeopardizing their relationship with St. Vincent’s Hospital or the University of New South Wales.

### Randomization

Eligible participants accepted into the program will be randomly allocated to either CBM Version A (Group 1 - active condition) or CBM Version B (Group 2 - control condition) based on an allocation sequence generated by an independent person not involved in the study, via a true randomization process (http://www.random.org). Numbers corresponding to treatment group (1 or 2) will be placed in sealed opaque envelopes with the sequential order number written on each envelope to ensure participants are allocated according to the pre-determined sequence. Participants remain blind to treatment group allocation. A member of the research team will open the envelope after all screening procedures have occurred and after the diagnostic interview has been conducted.

### Interventions

#### Cognitive bias modification program (both active and control conditions)

There are four separate sessions of the CBM program, each of approximately 20 to 30 minutes duration. These are completed over the course of five consecutive days (allowing some flexibility to delivery). Both conditions include four days of 164 training scenarios; with each CBM session delivering 41 training scenarios. The CBM training modules were created based on the methodology of Clerkin and Teachman [28] and have been validated in Williams and Grisham [30]. Scenarios are based on the individual items of the OBQ-44 and tap the broad belief domains of Tolerance for Uncertainty, Threat Estimation, Control of Thoughts, Importance of Thoughts, Responsibility and Perfectionism. Participants are asked to read and imagine themselves in various scenarios that could potentiate a negative OC interpretation. Each training scenario is immediately followed by a comprehension question to ascertain compliance with the training instructions. Adherence to the daily CBM sessions will be automatically tracked by the computer program. Standardized email reminders will be sent to a participant if more than two days lapse between logins.

#### Active cognitive bias modification

In this version (the intervention condition) all scenarios have a positive resolution, designed to induce a positive interpretation bias to ambiguous information. For example: ‘You are riding the bus home from work. The passenger beside you sneezes so you offer them a tissue. You think to yourself that offering a tissue was a behavior that was k_nd/’ (requiring the participant to enter the letter ‘i’ to form the word ‘kind’). The scenario completion task was followed by a comprehension question to ensure the participant had processed the meaning of the sentence ‘Are you pleased that you offered a stranger a tissue?’ (YES). In this condition a specific learning contingency is established between the ambiguous start of the scenario and the imagined positive resolution.

#### Control cognitive bias modification

In this version (the control condition) the scenarios are identical in content but are not designed to induce a positive interpretation bias: 50% of the scenarios resolve in a positive manner, 50% of the scenarios resolve in a negative manner. Therefore, no contingency is established between the start of the scenario and the valence of the imagined final resolution. For example, the negative resolution of the scenario above would be as follows: ‘You think to yourself that offering a tissue was a behavior that was r_sky’ (requiring the participant to enter the letter ‘i’ to form the word ‘risky’). The comprehension question corresponding to a negative resolution would be as follows: ‘Are you pleased that you offered a stranger a tissue?’ (NO).

### Procedure

After completion of the informed consent process and enrollment, participants will be sent a link via email to complete the online self-report questionnaires. Participants will then be sent an email with instructions to access the online CBM training modules. Following completion of the final module participants will complete the post-CBM questionnaires (at Day 8). Participants will be contacted after one month to complete the follow-up measures (the primary baseline measures) and telephoned to complete the OCD M.I.N.I Module diagnostic interview.

### Primary outcome measures

#### The Obsessive Compulsive bias measure [28]

To obtain an index of interpretation bias both before and after CBM-I training, the bias measure designed by Clerkin and Teachman [28] will be employed. Participants are first exposed to ten scenarios with a missing letter in the final word of the sentence. Each scenario remains ambiguous in nature even after completion of the word fragment (for example, ‘You are driving to visit friends who live several hours away. Outside, it begins to rain and you are careful to drive the speed limit. You think about the importance of driving s_fely’). In this example, the letter ‘a’ would be required to complete the word stem of ‘safely’. Following the filler task (below), participants are randomly presented with four sentences and required to rate how similar each was to the meaning of the scenario they previously imagined themselves in (1 = very different in meaning to 4 very similar in meaning). Each sentence corresponds with four different interpretations, none of which was worded identically to the sentence in the paragraph they had previously imagined themselves in. OC-positive scenarios are consistent with a response that challenges the core maladaptive belief (for example, ‘As you drive down the road, you think your chances of getting into an accident are low because you are being so cautious’) whereas OC-negative scenarios are those consistent with a response that reinforces the core maladaptive belief (for example, ‘*As you drive down the road, you worry that you’ll accidentally crash your car even though you aren’t speeding’*). Foil scenarios are included to assess for a general interpretation bias. Foil Positive scenarios are positive, but unrelated to core OC maladaptive beliefs (for example, ‘*As you drive down the road, you are looking forward to visiting your friend’*) and Foil Negative scenarios are negative, but also unrelated to OC beliefs (for example, ‘As you drive down the road, you are not looking forward to visiting your friend*’*). Cronbach’s alpha for the indices ranges from .68 to .79. The OC Bias Measure will be administered at baseline, following the 1-week CBM intervention, and at 1-month follow-up.

#### Ambiguous Scenarios Test-obsessive compulsive disorder

The AST-OCD (AW and JG, unpublished work) is a measure of interpretation bias comprising 12 ambiguous scenarios designed to tap the following belief domains: intolerance of uncertainty, perfectionism, threat estimation, control of thoughts, responsibility, and importance of thoughts. Each belief domain comprises two items. Items are rated in terms of their emotional valence (1 = very negative to 7 = very positive) and their associated arousal (1 = very anxious to 7 = very excited). Scores are averaged to form a total score of valence and arousal. Participants are asked to imagine each of the scenarios and imagine the event happening to them (for example, ‘Your partner has taken you to a new restaurant for dinner. Before you eat, you visit the restroom and notice it is unusual’). The AST-OCD will be collected at baseline, following the 1-week CBM intervention, and at 1-month follow-up.

#### The obsessive beliefs questionnaire-TRIP [33]

The OBQ-TRIP (20-item version) is a factor-analytically derived brief version of the original Obsessive Compulsive Cognitions Working Group (OCCWG) 44-item version [18]. Each of the 20 items designed to measure cognitions and beliefs central to OCD are rated on a 7-point Likert-type scale (1 = disagree very much to 7 = agree very much). The OBQTRIP- 20 correlates well with the full OBQ-TRIP and demonstrates good internal consistency, Cronbach’s alpha = .77 to .82 [18]. The OBQ-TRIP will be collected at baseline, following the 1-week CBM intervention, and at 1-month follow-up.

### Secondary Outcome Measures

#### The dimensional obsessive-compulsive scale [34]

The DOCS is a 20-item self-report measure that assesses the severity of the four most consistently replicated OCD symptom dimensions (a) contamination, (b) responsibility for harm and mistakes, (c) symmetry/ordering, and (d) unacceptable thoughts. Items are rated on a 5-point scale, with scores for each symptom dimension range from 0 (minimum) to 20 (maximum) and total scores ranging from 0 to 80. To accommodate the heterogeneity of OCD symptoms, and the presence of obsessions and rituals within each symptom dimension, each subscale begins with a description of the symptom dimension along with examples of representative obsessions and rituals. The examples clarify the form and function of each dimension's fundamental obsessional fears, compulsive rituals, and avoidance behaviors. Within each symptom dimension, five items (rated 0 to 4) assess the following parameters of severity (over the past month): (a) time occupied by obsessions and rituals, (b) avoidance behavior, (c) associated distress, (d) functional interference, and (e) difficulty disregarding the obsessions and refraining from the compulsions. The DOCS demonstrates excellent psychometric properties and the subscales have excellent reliability in clinical samples (*α* = .94 to .96; in current sample *α* = .93 to .96), and the measure converges well with other measures of OC symptoms [34]. The DOCS will be collected at baseline, following the 1-week CBM intervention, and at 1-month follow-up.

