#### Kessler-10 psychological distress scale [40]

The K10 consists of 10 items ranked on a five point scale designed to measure non-specific psychological distress. For the current study, the time-frame was modified to assess psychological distress in the past week rather than in the past 30 days. The K10 possesses strong psychometric properties [40].

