### Statistical methods

Significance testing of group differences regarding demographic data and pre-treatment measurements will be conducted using ANOVA and χ2 where the variables consist of nominal data. Intent-to-treat (ITT) mixed models using restricted maximum likelihood (REML) estimation will be used to account for missing data due to participant drop-outs. Significant effects will be followed up with pairwise contrasts comparing pre-treatment to post-treatment scores. Complete-case analyses of the primary hypotheses using data from participants who complete all four sessions of the CBM program will also be conducted. The effect of potential treatment moderators will be evaluated by including baseline variables of interest as a covariate and interaction term in separate mixed models analyses. Analyses will be performed in SPSS. Effect sizes will be calculated between groups (Hedges *g*) and within groups (Cohen’s *d*, adjusting for the repeated measures correlation) using the pooled standard deviation and adjusted for sample size.

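### The Day-8 DOCS asks about the past month, so most of its recall window precedes training and the pre-to-post symptom comparison is diluted towards no effect

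*Protocol article*

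**What the plan says.** All places are in the protocol article.

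- **Recall window.** The DOCS section states that within each symptom dimension "five items (rated 0 to 4) assess the following parameters of severity (over the past month").
- **Visits.** The same section states: "The DOCS will be collected at baseline, following the 1-week CBM intervention, and at 1-month follow-up".
- **Timing of the post-treatment visit.** Procedure: "Following completion of the final module participants will complete the post-CBM questionnaires (at Day 8").
- **Length of training.** The section on the program common to both conditions says of the four sessions: "These are completed over the course of five consecutive days", with some flexibility.
- **Hypothesis.** For participants with current OCD, the Hypotheses section predicts that active training lowers OC symptom measures relative to control, and then that benefits persist to 1 month. It names the DOCS as the symptom measure when it predicts no significant change in the lifetime-only group.
- **Analysis.** Statistical methods plans intention-to-treat mixed models by REML, with significant effects followed up by "pairwise contrasts comparing pre-treatment to post-treatment scores".
- **A contrasting choice.** For the Kessler-10, "the time-frame was modified to assess psychological distress in the past week rather than in the past 30 days". No reason is given, and no such change is described for the DOCS.
- **Follow-up battery.** Procedure says participants are contacted after one month "to complete the follow-up measures (the primary baseline measures").

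**The concern.** A scale that asks about the past month cannot respond fully to something that began a week ago. Most of what a participant is asked to summarise at Day 8 happened before the first session, and most of it was already rated at baseline. Both arms share that pre-training period, so it pulls the arms together.

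Symptom reduction is one of the two effects predicted for current OCD, and the DOCS is the only OC symptom severity scale in the battery. The hypotheses place the effect before the 1-month visit, and the one contrast named is pre to post, so the plan as written looks for the symptom effect at the visit where the instrument is least able to show it. A null there could mean that training has no effect on symptoms, or that the recall window has hardly been exposed to training. The same ambiguity affects the lifetime-only group, where a null is the prediction and the window pushes in its favour.

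**Working it through.** **Inputs.** Recall window L: past month, taken as 28 to 31 days (assumption). Post-treatment visit: Day 8. Training: Days 1 to 5, with Day 1 as the first session (assumption; the article does not define Day 1).

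**Step 1: share of the Day-8 window after training.** Share = days elapsed / L. From the first session to Day 8 is 7 days, or 8 counted inclusively. From the end of training on Day 5 it is 3 days.

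| L (days) | 7 days after first session | 8 days, inclusive | 3 days after Day 5 |
|---|---|---|---|
| 28 | 25.0% | 28.6% | 10.7% |
| 30 | 23.3% | 26.7% | 10.0% |
| 31 | 22.6% | 25.8% | 9.7% |

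The share before the first session is 100% minus columns two and three: from 100 − 28.6 = 71.4% to 100 − 22.6 = 77.4%, or 22 to 23 of 30 days. About 90% precedes the end of training. If baseline is completed shortly before the first session, these pre-training days are nearly all within the baseline window too.

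**Step 2: the same check at 1 month.** Counted from Day 8, a one-month window reaches back only to Day 8, after training ended. Counted from Day 1, it reaches back to about Day 1: it contains the five training days (5/31 = 16% to 5/28 = 18%) but essentially no pre-training days.

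**Step 3: what dilution could do (illustration only).** The article gives no expected DOCS effect. Its only planning effects are 0.66 and 0.76, from interpretation-bias outcomes. Its minimum of 29 per group is reproduced by d = 0.76, two-sided alpha 0.05, power 0.80 with a t-test (28.17, rounded up). Borrow these values for the DOCS, and suppose that respondents average evenly over the month and that the effect is complete from Day 1. Then visible d = true d × share. With L = 30:

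- true d 0.66: 0.66 × 7/30 = 0.154 to 0.66 × 8/30 = 0.176; two-sided power at 29 per arm 9% to 10%
- true d 0.76: 0.177 to 0.203; power 10% to 12%
- undiluted, at 29 per arm: 69% (0.66) and 81% (0.76)

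Those are unadjusted comparisons at a single visit, whereas the plan models repeated measures. With baseline adjustment, the non-centrality is d × √(n/2) / √(1 − r²). For d = 0.165 and n = 28, d × √14 = 0.617. Assumed baseline correlations of 0.7, 0.8 and 0.9 give 0.86, 1.03 and 1.42, hence power of about 14%, 18% and 29% (normal approximation).

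**The case against.** The strongest reply is that the unaffected measurement is already in the plan: the DOCS section schedules the scale at 1 month, and nothing confines the mixed model to two visits. The pre-to-post contrasts only follow up significant effects, and an article may leave the full list of contrasts to an analysis plan. This stands to the extent that a reader should not infer that the symptom hypothesis cannot show an effect anywhere in this trial. It does not remove the point, because the article itself fixes the recall window, the visit day, the role of 1 month as maintenance and the pre-to-post contrast, and these do not fit together.

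Three other stronger readings are tempting and not supported:

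- **That power for symptoms is about 10%.** That figure borrows an effect size from a different construct, assumes even averaging over the month, and ignores the planned model. Overlapping windows also raise the pre-post correlation, which recovers some precision. If recent days weigh more, the dilution is smaller.
- **That the authors saw the recall problem and fixed it only for the Kessler-10.** The article reports that change without a reason. The difference in treatment is fair to note; a motive is not.
- **That the DOCS will not be collected at 1 month.** The parenthesis in Procedure may simply mean the main baseline battery, and the sections on the DOCS, PHQ-9 and WSAO each schedule a secondary scale at that visit. It is an ambiguity of wording.

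It is also true that the DOCS is secondary, so the primary bias outcomes and the sample size are untouched, and that the dilution does not create false positives.

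**Conclusion.** The point holds in a limited form. At Day 8 about 71% to 77% of the DOCS recall window precedes the first session and overlaps the baseline rating, so the between-arm comparison there is biased towards no difference. The direction follows from the stated window and visit day, provided respondents give the earlier weeks some weight. The percentages rest on a 28-to-31-day month and on Day 1 being the first session. The size of the loss cannot be derived from the article; the power figures above only illustrate it.

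The practical consequence is that a null Day-8 DOCS result would not be evidence that training leaves symptoms unchanged, while the plan's wording directs the symptom test to that visit. This deserves correction because the remedy is cheap, but it concerns one of three visits for a secondary outcome.

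**What to change.** 1. In Hypotheses and Statistical methods, name the between-arm difference in DOCS change from baseline to 1-month follow-up, estimated from the planned mixed model, as the main test of the symptom hypothesis. The DOCS remains a secondary outcome.
2. Report the Day-8 DOCS as descriptive, with a sentence saying that its recall window lies mostly before training and that a null there is not evidence of no symptom effect.
3. In Procedure, replace the reference to the primary baseline measures with a list of the scales repeated at 1 month, including the DOCS, so that it agrees with the DOCS section.

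These are wording changes. They need no new data and do not disturb the baselines of the 28 participants randomized by the time of submission. They should be dated and made before any comparison by arm. The downside is that data are likely to be somewhat less complete at 1 month than at Day 8.

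Switching the DOCS to a past-week instruction is not recommended at this stage: it would depart from the past-month form the protocol describes and break comparability with baselines already collected.
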